#### Sample size and power calculation

Sample size was calculated for the primary endpoint (SF-12v2 PCS week 26). Additional power calculations were performed for the co-primary endpoint (VAS pain score week 26). Within the German norm population, mean SF-12v2 PCS is 50 and the standard deviation is 10 [18]. The study population is expected to come very close to this German norm population. Based on the inclusion criteria (age between 18 and 65) and demographic data of the proximal tibia fractures treated at the trial site in Mainz between 2009 and 2011, it seems justified to expect the SF-12v2 PCS results 26 weeks after surgery to be 50 ± 10 (mean ± standard deviation) in both treatment groups. The non-inferiority margin was defined as 5 points on the SF-12v2 PCS scale (range: 0–100). This value is half of the expected standard deviation in the reference population. Since changing one of the SF-12v2 items affecting SF-12v2 PCS by one category causes SF-12v2 PCS to change by at least 3 points, the non-inferiority margin corresponds to less than two items changed by one response category. Under these assumptions, a shifted two-sample t-test with a one-sided significance level of 2.5% and a power of 80% requires 128 patients to show that mean SF-12v2 PCS 26 weeks after surgery in patients treated with CBVF is not more than 5 points lower compared to the control group. Since 5% of randomized patients are expected to be ineligible for the primary Per Protocol Analysis, 136 patients will be randomized. Pain assessed by VAS after 26 weeks is expected to be 2 (80%) or 1 (20%) in the control group and 2 (10%), 1 (20%) or 0 (70%) in the CBVF treatment group. Based on these assumptions, the probability that pain assessed on a VAS comparing one randomly selected patient in each group is higher in the patient treated with CBVF is 14%. A Wilcoxon-Mann–Whitney-Test comprising 128 patients will have a power of >99% to show at a two-sided significance level of 5% that the above specified probability is <50%.

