### Analysis populations

The intention to treat (ITT) population comprises all randomized patients, even if the planned surgery/surgeries did not take place. The modified intention to treat (mITT) population includes all randomized patients for which the primary endpoint could be assessed (that is, SF-12 PCS assessment is available both preoperatively and 26 weeks after surgery). Patients are eligible for the per protocol (PP) population, if they fulfill the following criteria: eligible for the mITT population, no violation of inclusion criteria, not meeting any exclusion criteria, trial treatment as randomized, time interval between Visit 2 (day 0, surgery) and Visit 7 (week 26): 22 to 30 weeks, absence of events with a strong effect on quality of life but definitely unrelated to the randomized study treatment (for example, new serious disease during post-operative follow-up, or accident).

The safety population comprises all randomized subjects who received trial treatment (autologous bone graft or Treatment with CBVF). In analyses of the safety population, subjects will be assigned to the treatment they actually received.

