### Efficacy analysis

Within the primary analysis of this study, SF12v2 summary scores are not normalized to the reference population. Nevertheless, normalized z and t scores of SF12v2 summary scores will be calculated in explorative analyses. SF-12v2 standard 4-weeks recall version will be used within this study. The confirmatory efficacy analysis is planned using a hierarchical testing procedure. In the first step, differences between SF-12v2 PCS are tested by an analysis of covariance (ANCOVA) with SF-12v2 PCS at week 26 as the dependent variable and SF-12v2 PCS at screening, age group (18–39; 40–65), gender, and treatment as covariates. If the covariate-adjusted two-sided 95% confidence interval of the treatment effect within this model (difference of SF-12v2 PCS, experimental treatment group - control group) is located completely above the non-inferiority margin of −5, non-inferiority of CBVF with respect to Physical Component of Quality of Life 26 weeks after surgery will be claimed. The primary endpoint will be primarily analyzed in the PP population. Only if non-inferiority can be claimed in the first step, pain as the co-primary endpoint may be tested in a confirmatory way. Differences between pain assessed by VAS 26 weeks after surgery will be tested by a Wilcoxon-Mann–Whitney-U-Test at a two-sided significance level of 5%. Analysis will be done primarily for the mITT population. Within this hierarchical testing procedure, a global significance level of 5% is ensured. The power was not adjusted since the local power of the second test (pain assessment) is sufficiently large (>99%). In order to check robustness of confirmatory results, supportive analyses of both (co-)primary endpoints will be performed in the mITT, PP and ITT populations. Models with a modified set of covariates (for example, trial site and surgical technique) will also be calculated as supportive analyses. Analyses in the ITT population will require imputing missing data. Multiple imputation methods are planned within this context. Further details will be specified in the Statistical Analysis Plan. All secondary endpoints will be analyzed using appropriate methods depending on the scale of the respective parameter. Analyses of secondary endpoints will be interpreted exploratively.

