### Source of bias

To reduce ascertainment bias, QOL and pain assessments will be performed by independent surgeons who will not be directly involved in the operative treatment of the patients. Furthermore, the assessments will be performed by persons with broad experience in treating trauma patients to determine whether or not events impacting QOL are really related to the treatment. The assessors will document all relevant events potentially impacting QOL and pain in the trial report. However, a consequent blinding of the assessors will not be feasible, since an additional wound will be obvious in all patients of the autologous bone graft group. Therefore, the method of assessment may be associated with an ascertainment bias, which cannot be avoided completely by the study design.

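### The per-protocol interval alone decides non-inferiority, although membership of that set rests partly on a subjective post-randomisation criterion in an open-label trial

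*Protocol article*

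**What the plan says.** **Decision rule.** Under Efficacy analysis, step 1 claims non-inferiority if the ANCOVA-adjusted two-sided 95% confidence interval for CBVF minus control in week-26 PCS lies wholly above -5. The deciding set is fixed there: "The primary endpoint will be primarily analyzed in the PP population". Pain becomes confirmatory only if step 1 succeeds. For robustness, "supportive analyses of both (co-)primary endpoints will be performed in the mITT, PP and ITT populations", with multiple imputation planned for ITT. Nothing says what follows if these disagree with PP.

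**Who is in PP.** Under Analysis populations, PP needs a PCS before surgery and at week 26, eligibility, treatment as randomised, a final visit at 22 to 30 weeks, and "absence of events with a strong effect on quality of life but definitely unrelated to the randomized study treatment". New serious disease and an accident are the examples given.

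**Who judges relatedness.** Source of bias says that experienced assessors, not involved in the operation, are used "to determine whether or not events impacting QOL are really related to the treatment". It adds that "a consequent blinding of the assessors will not be feasible", because the graft arm has an additional visible wound, and it concedes some ascertainment bias. The only blinded review described in the article is that of the images.

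**The concern.** Most PP criteria can be checked against a date or a record. The quality-of-life event criterion is different: it acts after randomisation, it selects patients likely to have a low score on the primary endpoint, and it turns on an opinion about causation formed with the arm known. If doubtful events were called unrelated more readily in the CBVF arm, low CBVF scores would leave the analysis and the estimated difference would move away from -5.

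Such a shift matters more because no second analysis has to agree. If PP passed and ITT failed, the text would still permit the claim and the confirmatory pain test. The 5% global level that Efficacy analysis says is ensured therefore depends on PP exclusions being uninformative, and the described procedures do not protect that condition.

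**Working it through.** **1. Inputs from Sample size and power calculation.** "The non-inferiority margin was defined as 5 points on the SF-12v2 PCS scale"; "SF-12v2 PCS results 26 weeks after surgery to be 50 ± 10 (mean ± standard deviation) in both treatment groups", so the SD is 10 and the planned true difference 0; one-sided 2.5%; 136 randomised with 5% expected to be ineligible for PP. The allocation ratio is not stated; 1:1 (68 per arm) is assumed.

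**2. The plan's own figure.** The text says "a shifted two-sample t-test with a one-sided significance level of 2.5% and a power of 80% requires 128 patients". The exact noncentral t calculation gives 79.5% power at 126 patients and 80.15% at 128, so 128 reproduces. Then 128 / 0.95 = 134.7, that is 135, or 136 with equal arms. The exclusions budgeted, for all reasons and in both arms, are about 7 to 8: 0.05 × 136 = 6.8, and 136 − 128 = 8.

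**3. Analytic scenario at the margin (true difference -5).** Suppose a net k of 68 CBVF patients leave PP and score 15 points below the other CBVF patients (k, arm and 15 points are all assumed).

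- Shift = 15 × k / 68
- SE = 10 × √(1/(68 − k) + 1/68)
- False non-inferiority rate = 1 − Φ(1.96 − shift / SE)

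| k | Shift | SE | False non-inferiority |
|---|---|---|---|
| 0 (or balanced) | 0 | 1.715 | 2.5% |
| 2 | 0.44 | 1.728 | 4.4% |
| 4 | 0.88 | 1.742 | 7.3% |

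**4. Simulation at the margin.** 40,000 trials, 68 per arm, SD 10, unadjusted 95% confidence interval, exclusions from the CBVF arm only.

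| CBVF patients removed | At random from the lowest third | The lowest scores (extreme case) |
|---|---|---|
| 0 | 2.4% | 2.5% |
| 2 | 3.7% | 6.2% |
| 4 | 5.7% | 11.9% |
| 8 | 12.6% | 27.4% |

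The last row spends the whole exclusion budget on one arm and one kind of patient, so it is a bound and not an expectation.

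**5. Effect of requiring both sets.** A claim that needs both intervals cannot be made more often than the all-randomised interval passes. In the simulation, the error at the margin under the joint rule stayed between 2.4% and 2.7% whatever was removed from PP. At a true difference of 0, with 136 complete patients and 4 random PP exclusions per arm, power was 82.4% for all randomised, 80.1% for PP, and 78.5% for both.

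**The case against.** A PP primary analysis is common in non-inferiority trials, and a reader might infer that choosing PP is the error. The documents do not support that. Excluding patients not treated as randomised usually guards against false non-inferiority, because crossovers make the arms look alike.

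A reader might also infer that the unblinded assessors decide who is in PP. Source of bias says that they judge relatedness and document events; Analysis populations does not say who applies the criterion, when, or with what masking. The SAP, to be finalised before database closure, could provide for a masked data review.

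The criterion is also narrow. It needs a strong effect and certainty that treatment was not the cause, so possibly related events stay in. Truly unrelated events should fall on both arms by chance. Bias needs misjudged events, mainly in one arm.

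Finally, the ITT results will be reported, so a disagreement would be visible, and pain is analysed primarily in mITT, so PP exclusions affect only whether the pain test is opened and not the pain estimate.

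All of this stands and limits the point. It does not remove it: reporting a discordant ITT result is not a rule that blocks the claim, and the deciding set is fixed in the protocol rather than left to the SAP.

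**Conclusion.** The point holds in a limited form. The PP interval is the sole decider for step 1, and PP membership depends in part on a causal judgement that is open to knowledge of the arm. Either feature alone would be tolerable; together they leave the confirmatory claim unprotected against informative exclusion.

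The size is a range that starts at no inflation: 2.5% if exclusions are balanced or unrelated to score, about 4.4% to 7.3% for a net 2 to 4 low-scoring CBVF patients, and about 12% if the four lowest CBVF scores go. The article gives no count, arm or score for such exclusions, so these figures show what the rule would allow. They are not evidence that the trial's error rate is inflated. The calculations use an unadjusted comparison with SD 10 and 1:1 allocation.

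**What to change.** 1. In Efficacy analysis, state that non-inferiority is claimed, and step 2 opened, only if the two-sided 95% confidence interval for the PCS difference lies above -5 in both the PP set and the ITT set, the latter with the multiple imputation already planned. ITT is a better companion than mITT, which also drops patients without a preoperative or week-26 PCS.
2. In Analysis populations, strike the criterion on unrelated quality-of-life events, or state that it is decided from arm-masked event narratives before database closure.

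**Cost.** Both analyses are already planned, so no new data are needed. Under Pre-specification, a major change to the primary endpoint analysis must also appear in a protocol amendment, and Trial status gives the trial as recruiting. Power with both sets required is about 78.5% against 80.1% for PP alone (136 complete patients, true difference 0), slightly under the planned 80%. The power statement should be restated, allowing for missing PCS data in the ITT analysis.

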### Randomization

After giving consent to participate in the study, patients will be randomized by a web-based randomization tool provided by IZKS Mainz allowing investigators to randomize patients via a secure web interface. Randomization will be stratified by age group (18 to 39 years; 40 to 65 years) and gender. Block randomization with variable block sizes will be applied.

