#### V1 - screening visit and randomization

The trial aims and procedures will be explained to the patient by responsible local investigators using a study information booklet. After informed consent is given, the screening visit (V1) will be performed within 7 days prior to day of surgery (day 0). After radiological assessment of the fracture type, baseline demographics, comorbidity, medication, and pregnancy test (if applicable) will be evaluated and verification of inclusion and exclusion criteria performed. The trial participant will be electronically randomized to one of the two treatment arms using a web-based tool. All data will be documented using an electronic case report form (eCRF). Assessment of the VAS and SF-12v2 scores will be performed at the end of the V1.

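### The confirmatory pain test ignores the randomisation strata and baseline VAS; adjusting for the strata is an optional, nearly free gain that matters only if the pain effect is far smaller than assumed

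*Protocol article*

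**What the plan says.** The Efficacy analysis section sets a two-step hierarchy. Step 1 is an ANCOVA of week-26 PCS with screening PCS, age group, gender and treatment in the model. Step 2, reached only if step 1 shows non-inferiority, is the pain comparison: "Differences between pain assessed by VAS 26 weeks after surgery will be tested by a" Wilcoxon-Mann-Whitney U test, "at a two-sided significance level of 5%. Analysis will be done primarily for the mITT population". No baseline value or stratum is named for step 2.

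The information needed for adjustment exists. Under Randomization: "Randomization will be stratified by age group" (18 to 39 or 40 to 65 years) and by gender. Under V1: "Assessment of the VAS and SF-12v2 scores will be performed at the end of the V1".

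The Sample size and power calculation section sizes the trial on PCS. For pain it assumes VAS scores "expected to be 2 (80%) or 1 (20%) in the control group" and "2 (10%), 1 (20%) or 0 (70%) in the CBVF treatment group", and concludes that the test "comprising 128 patients will have a power of >99" per cent.

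The Efficacy analysis section also plans supportive analyses of both (co-)primary endpoints and models with other covariates, with trial site and surgical technique as examples. It names no adjusted analysis for pain.

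**The concern.** The two confirmatory tests treat the same design differently, and no reason is given. Stratified randomisation balances age group and gender between the arms. If either predicts week-26 pain, an unadjusted test still counts that between-stratum variation as noise, so it is slightly conservative and less powerful than a test that respects the strata. A baseline score that predicts the outcome has the same potential, usually a larger one.

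Pain is the trial's only confirmatory superiority claim and it has one test. The stated power rests on assumed distributions with almost no spread and a very large group difference, for which the article cites no source, although it cites one for PCS. If the true effect is much smaller, the choice of test starts to matter.

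**Working it through.** **Inputs from the protocol.** 128 analysed patients; two-sided 5%; control VAS 2 (80%) or 1 (20%); CBVF VAS 2 (10%), 1 (20%) or 0 (70%). The article does not state the allocation ratio; 1:1 is assumed, giving 64 per arm.

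**Step 1: reproduce the planned effect.**
- P(CBVF higher) = 0.10 × 0.20 = 0.02.
- P(tie) = 0.10 × 0.80 + 0.20 × 0.20 = 0.12.
- Mann-Whitney probability with ties split: θ = 0.02 + 0.12/2 = 0.08.
- The protocol says the probability that pain "is higher in the patient treated with CBVF is 14" per cent. That is 0.02 + 0.12, the probability of higher *or equal* pain. Power is computed below at both values, and the difference does not matter.
- Means: control 2 × 0.8 + 1 × 0.2 = 1.8; CBVF 2 × 0.1 + 1 × 0.2 = 0.4. Variances: 0.16 and 0.44. Standardised difference: 1.4 / √((0.16 + 0.44)/2) = 1.4 / 0.548 ≈ 2.6.

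**Step 2: reproduce the stated power.** Noether's formula at 1:1 is power = Φ(√(3N) × |θ − 0.5| − 1.96).
- θ = 0.14: √384 × 0.36 − 1.96 = 7.05 − 1.96 = 5.09; power 0.9999998.
- θ = 0.08: √384 × 0.42 − 1.96 = 6.27; power above 0.999999.
- Simulating the tie-corrected test from the stated distributions gives 1.000 at N = 128 and already 99.3% at N = 20.

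The stated >99% reproduces. At this effect, adjustment with any assumed correlation from 0 to 0.6 adds 0.00 points.

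**Step 3: a smaller effect, by formula.** Choose θ = 0.357, where the plain test has √384 × 0.143 − 1.96 = 0.84, that is 80% power. Adjustment for information with correlation ρ to week-26 VAS acts like N = 128/(1 − ρ²):

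| assumed ρ | power | gain (points) |
|---|---|---|
| 0 | 80.0% | – |
| 0.1 | 80.4% | 0.4 |
| 0.2 | 81.6% | 1.6 |
| 0.3 | 83.6% | 3.6 |
| 0.4 | 86.4% | 6.4 |
| 0.5 | 89.9% | 9.9 |

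**Step 4: a smaller effect, by simulation.** Assumptions: 64 per arm, shift 0.45 SD, baseline correlation 0.1 to 0.5, strata R² 2 to 10%. The plain test has about 70% power.
- Strata alone: gain of about 0 to 3 points.
- Strata plus baseline VAS: gain of about 1 to 14 points. For example, 70% rises to 75% at correlation 0.3 and R² 5%. The top of the range needs correlation 0.5 and R² 10%; separate runs of that setting gave 15 to 16 points, so the upper end is approximate.
- Under no effect, the plain test rejected in 4.2 to 4.6% of runs and all tests stayed near 5%.

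**Step 5: would a wider spread alone be enough?** Keep the planned means of 1.8 and 0.4 on an assumed 0 to 10 scale. The largest possible variances, with every patient at 0 or 10, are 1.8 × 8.2 = 14.76 and 0.4 × 9.6 = 3.84. The pooled SD is then √9.3 = 3.05, and 1.4/3.05 = 0.459. So the planned means cannot give a shift as small as 0.45 SD on that scale. With beta-binomial scores of SD 3.2 and 1.6 around those means, the plain test still had 95.6% power. The scenarios in steps 3 and 4 therefore need a smaller mean difference than planned.

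**The case against.** The strongest defence is that nothing is broken. The plain rank test is valid, prespecified, suited to coarse and tied scores, and the same test for which power was computed. That stands. A reader might infer that the trial throws away power it has paid for; the documents do not support this. The sample size comes from PCS, and planned pain power is already above 99%. A reader might also infer that the test is wrong because it omits the strata; at most it is slightly conservative.

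Second, the gains rest on assumptions with no basis in the documents: an effect far below plan, and a sizeable correlation between pain recorded within days of an acute fracture and pain half a year later. This stands too. At correlations of 0.1 to 0.3 the gain in step 3 is only 0.4 to 3.6 points.

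Third, baseline VAS may not be a clean covariate. The V1 section describes randomisation and then places the VAS at the end of the visit, in an open-label trial, so patients may score their pain already knowing their allocation. This stands and limits the fix. Without baseline VAS, only the strata gains apply.

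Fourth, an adjusted pain analysis could sit among the supportive models. It could, but none is named, and a supportive analysis does not alter the confirmatory test.

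**Conclusion.** The inconsistency is real: step 1 of the hierarchy uses its baseline and both strata, and step 2 uses neither. Its practical weight is small. At the protocol's assumed effect the gain from adjustment is nil. If the effect is much smaller (0.45 SD, 64 per arm), it is about 0 to 3 points from the strata alone and about 1 to 14 points with baseline VAS added. The shift, the correlation, the strata R² and 1:1 allocation are all assumptions. This is an optional improvement in efficiency and consistency; the validity of the pain test is not in question.

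**What to change.** Before database closure, and without sight of pain results by arm, name one of the following as the confirmatory pain test: a van Elteren test stratified by age group × gender, or a rank ANCOVA of week-26 VAS on treatment, age group and gender. Add baseline VAS to the rank ANCOVA only if it is confirmed that the score was recorded before randomisation; otherwise leave it out. Keep the plain Wilcoxon-Mann-Whitney test as a sensitivity analysis.

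The cost is wording in the SAP and, because a co-primary analysis changes, a protocol amendment in line with the Pre-specification section. Standard SAS code is enough, and no new data or patients are needed. The one extra task is to establish the order of VAS and randomisation at V1, if baseline VAS is to be used.

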**Methods/Design:**

CERTiFy (CERament™ Treatment of Fracture defects) is a prospective, multicenter, controlled, randomized trial. We plan to enroll 136 patients with fresh traumatic depression fractures of the proximal tibia (types AO 41-B2 and AO 41-B3) in 13 participating centers in Germany. Patients will be randomized to receive either autologous iliac crest bone graft or CBVF after reduction and osteosynthesis of the fracture to reconstruct the subchondral bone defect and prevent the subsidence of the articular surface. The primary outcome is the SF-12 Physical Component Summary at week 26. The co-primary endpoint is the pain level 26 weeks after surgery measured by a visual analog scale. The SF-12 Mental Component Summary after 26 weeks and costs of care will serve as key secondary endpoints. The study is designed to show non-inferiority of the CBVF treatment to the autologous iliac crest bone graft with respect to the physical component of quality of life. The pain level at 26 weeks after surgery is expected to be lower in the CERAMENT bone void filler treatment group.

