### Outcome measures

#### Primary outcome

The primary endpoint in this study is the SF-12 v2 Physical Component Summary (PCS) score (4 week standard recall version) at week 26 after the intervention. The co-primary endpoint is pain VAS measurement at week 26 after the intervention. The SF-12 is a subset from items of the SF-36, which is the most widely used generic health assessment questionnaire worldwide.

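### The confirmatory pain test is confined to patients with SF-12 scores at baseline and week 26, although it uses no SF-12 data

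*Protocol article*

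**What the plan says.** Under Primary outcome, the protocol article makes week-26 pain co-primary: "The co-primary endpoint is pain VAS measurement at week 26 after the intervention". The abstract gives the direction: "The pain level at 26 weeks after surgery is expected to be lower in the CERAMENT bone void filler treatment group".

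Under Efficacy analysis, pain comes second in a hierarchy: "Only if non-inferiority can be claimed in the first step, pain as the co-primary endpoint may be tested in a confirmatory way". The test is a two-sided 5% Wilcoxon-Mann-Whitney test with no covariates, and on the set the plan says "Analysis will be done primarily for the mITT population".

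Under Analysis populations: "The modified intention to treat (mITT) population includes all randomized patients for which the primary endpoint could be assessed". This is spelled out as meaning that "SF-12 PCS assessment is available both preoperatively and 26 weeks after surgery". The VAS is not part of the definition. The per-protocol set, which is primary for PCS, is a subset of mITT. The ITT set "comprises all randomized patients, even if the planned surgery/surgeries did not take place". For pain it is used only in supportive analyses, with multiple imputation.

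**The concern.** The mITT set is tailored to the PCS endpoint: the PCS ANCOVA needs a week-26 value and uses the screening value as a covariate. The pain test inherits that set but needs neither number. A missing SF-12 thus removes a patient whose pain outcome is known.

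Pain is the only endpoint on which superiority is to be claimed in a confirmatory way. Such a claim should rest on every randomised patient with the outcome, and an exclusion rule tied to another questionnaire weakens that for no gain. The rule also acts after allocation. The V1 section describes electronic randomisation first and then places the VAS and SF-12 at the end of the visit, and the trial is open-label. Completion of the baseline form could therefore in principle depend on the arm.

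A smaller, related point concerns PCS. Because the per-protocol set requires mITT membership, a patient with a known week-26 PCS leaves the primary non-inferiority analysis if only the baseline covariate is missing.

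**Working it through.** **1. Which patients are affected.** For a patient with a valid week-26 VAS, the two sections together give:

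| Baseline PCS | Week-26 PCS | In mITT | In primary pain test | Data the pain test needs |
|---|---|---|---|---|
| present | present | yes | yes | available |
| missing | present | no | no | available |
| present | missing | no | no | available |
| missing | missing | no | no | available |

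The last three rows are the affected group. In the second row the patient also leaves the PCS analysis with the primary outcome known.

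**2. How many.** The documents state no rate of missing SF-12. Table 1 schedules SF-12 and VAS together at V1 and V7, so a missed visit usually loses both. Under Sample size and power calculation, 5% is allowed for every reason for per-protocol ineligibility combined. I take that as a ceiling for patients with a VAS but without an SF-12:

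- 0% × 136 = 0
- 2% × 136 = 2.7, about 3
- 5% × 136 = 6.8, about 7

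**3. The plan's own figures.** The plan gives 128 patients for PCS, from a margin of 5, SD 10, one-sided 2.5% and 80% power.

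- Normal approximation: 2 × (1.960 + 0.842)² × 10² / 5² = 62.8, so 63 per arm (126 in total).
- Noncentral t: power is 79.5% at 63 per arm and 80.1% at 64 per arm, so 128 is reproduced.
- Loss allowance: 128 / 0.95 = 134.7, so 135, or 136 for equal arms (1:1 is assumed; no ratio is stated).

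For pain the plan gives power above 99% with 128 patients. Noether's formula is power = Φ(√(12 × N × ¼) × |0.5 − p| − 1.96). With the plan's p = 0.14:

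- N = 128: √384 × 0.36 − 1.96 = 5.09, power above 99.99%
- N = 108: √324 × 0.36 − 1.96 = 4.52, power above 99.99%
- N = 96: √288 × 0.36 − 1.96 = 4.15, power above 99.99%

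Simulating the plan's two pain distributions (4,000 trials per sample size, tie-corrected test), every trial was significant at each total N tried from 136 down to 40. Losing 7 patients does not matter for power.

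**4. Could exclusion distort the test?** This is illustrative; none of these rates comes from the documents. There are 68 per arm and no true difference, with pain 0, 1 or 2 about equally likely (0.33, 0.33, 0.34). Some of the patients scoring 2 are dropped, with 6,000 simulated trials per row.

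| Share of top-pain patients dropped | Expected number dropped | Type I error |
|---|---|---|
| none | 0 | 4.5% |
| 15% in both arms | 68 × 0.34 × 0.15 = 3.5 per arm | 5.2% |
| 15% in one arm only | 3.5 | 5.9% |
| 30% in one arm only | 68 × 0.34 × 0.30 = 6.9 | 12.1% |

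The last row uses the full ceiling of about 7 patients, all in one arm and all with the worst pain. That is an extreme pattern. Balanced exclusion leaves the error near 5%.

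**5. PCS.** After the 5% allowance, 136 × 0.95 = 129.2 patients remain against 128 required, a slack of about one. Two patients short of 128 (63 per arm) costs about 0.6 percentage points of power (80.1% to 79.5%).

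**The case against.** The case on the other side is substantial on size. The two questionnaires are completed at the same visits, so few patients should have one without the other. Power is untouched. The baseline form, although listed after randomisation, is still completed at screening, before surgery and beside the VAS, and nothing in the article suggests that completion differs by arm. The plan also has supportive ITT analyses of both endpoints with multiple imputation, where the excluded VAS values return. A single set for both co-primary endpoints is a recognisable choice, and requiring baseline PCS matches the stated ANCOVA. The proposed replacement is itself a set selected on data availability.

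All of this limits the consequence; none of it supplies a reason for the SF-12 condition in a test without SF-12 data. The supportive ITT analysis checks robustness but does not carry the confirmatory decision. A VAS-based set does still select on availability of the outcome, which is why the ITT imputation should stay beside it. It does remove the selection that is unrelated to pain.

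Three stronger readings are tempting and not supported:

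- A reader might infer that the arms will be unbalanced or the pain result biased. The article makes this possible but does not show it.
- A reader might put the loss at 10% or more. That is at least double the plan's allowance for all per-protocol ineligibility.
- A reader might add that incomplete SF-12 forms are dropped, or fault the set for not guaranteeing a VAS. The article gives no scoring rule for incomplete forms, and handling of a missing VAS is commonly left to the SAP.

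**Conclusion.** The mismatch is real and rests on stated text: the article fixes both the mITT definition and its use for pain, so this is not a gap left to the SAP. Its expected size is small, between none and about 7 of 136 patients with a usable pain score. That range assumes that patients with a VAS but without an SF-12 do not exceed the plan's overall 5% allowance. Power is not at stake, and distortion of the type I error needs exclusions that are strongly related to both arm and pain. What remains is an avoidable post-randomisation exclusion from the only confirmatory superiority test. It should be corrected because correction is nearly free, not because the result is shown to be at risk. The PCS point is a secondary improvement of the same kind.

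**What to change.** Define the primary pain set separately: all randomised patients with a week-26 VAS, analysed in the arm to which they were randomised, with no SF-12 condition. Keep the planned ITT analysis with multiple imputation as the sensitivity analysis for pain.

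Secondarily, for the PCS ANCOVA, let mITT (and hence per-protocol) membership require only the week-26 PCS, and impute a missing baseline PCS without regard to arm, for example by the overall mean.

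The cost is two definition sentences in the protocol and SAP. Since they concern the confirmatory analyses, they are best recorded in a protocol amendment before the database is closed. No extra data are needed, and the hierarchy, the tests and the sample size stay as they are.
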